### 8.4 Loss aversion incentive (deposit contract group)

In the loss aversion arm, study staff will ask participants if they would like to make a deposit of a certain amount, not exceeding US\$15. The amount of compensation given to participants for participating in baseline HIV testing (as described above in 8.1.1 Recruitment) will facilitate the ability of interested participants to make a deposit, as we have learned in the pilot study we conducted in 2017. Study staff will retain deposits securely and participants will receive a receipt indicating their deposit amount. Participants will be able to retrieve their deposit when they return for HIV testing at the 3-month study visit. Participants who attend the 3-month visit and retest HIV negative will be asked if they would like to make a second deposit of a certain amount, not exceeding US\$15, to retest a second time at the 6-month study visit. In addition to retrieving their deposit if they return for HIV testing, participants will also receive interest (not exceeding US\$5 at each retest visit) on each of their deposits. The possibility that participants will lose their deposit if they do not come for an HIV test within the pre-specified testing periods (3-4 months, and 6-7 months after randomization) will be communicated clearly by study staff; deposits from individuals who do not test will be retained by the study team and will be used for other study-specific activities. This aspect of deposit contracts is essential in order for the principle of loss aversion to have an impact on participants' HIV testing behavior. Our pilot study in 2017 showed that a large majority of individuals were willing to make deposits and that the system of providing receipts worked well.

Adaptive intervention: Following enrollment of 20% of the anticipated number of participants in the loss aversion group, the study investigators will determine the proportion of participants who have agreed to make a baseline deposit. In the event that <15% of loss aversion incentive group participants have agreed to make a deposit, the study investigators may reduce the deposit amount by up to 50% in the loss aversion group for the remaining duration of the Aim 3 trial.

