Study staff will emphasize the voluntary nature of the deposit contract and remind participants that they are not required to make a deposit. Participants who decline to provide a deposit at baseline will still be encouraged to come for an HIV test within the pre-specific testing periods (3-4 months, and 6-7 months), but will not receive any incentive for the return HIV test at 3-4 months. Participants who do not make a baseline deposit, but come for retesting at the 3-4 month visit, will have an opportunity to make a deposit at the 3-4 month visit to return for HIV retesting at 6-7 months.

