## Secondary outcomes:

- b) **HIV retesting uptake at 3-4 months following randomization.**
- c) **HIV retesting uptake at 6-7 months following randomization.**
- d) **HIV retesting uptake among deposit contract group participants who make deposits.** We will evaluate HIV retesting uptake among participants in the deposit contract group who agree to make a baseline deposit, a 3-4 month deposit, and those who agree to make a deposit at both study baseline and the 3-4 month study visit.
- e) **Cumulative incidence of HIV seroconversion:** We will compare the cumulative incidence of HIV infections in each study group over the 6-7 months of study participation following randomization.

Predictors and mediators: Participants' demographic and socio-economic characteristics, as well as HIV risk behaviors, will be recorded at the time of the baseline HIV test.

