### 8.7.2 Analysis

Primary analysis:

- (a) **HIV retesting uptake:** We will compare HIV retesting uptake (defined as the proportion of participants retesting for HIV at both 3- and 6-month study visits) between the study groups. We hypothesize that HIV retesting uptake among participants offered loss aversion incentives will be higher than uptake among men offered no incentive, and higher than uptake among men offered gain-framed incentives. We will test for significant differences in HIV retesting uptake between the following groups using the 2-tailed  $\chi^2$  analysis or other appropriate statistical methods: a) loss aversion vs. gain-framed incentive; b) loss aversion vs. no incentive; and c) gain-framed vs. no incentive.

Secondary analyses:

- (b) **HIV re-testing uptake at 3-months:** We will compare the proportion of participants who retest for HIV at the 3-month study visit between the study groups. We will test for significant differences in HIV retesting uptake between the following groups using the 2-tailed  $\chi^2$  analysis or other appropriate statistical methods: a) loss aversion vs. gain-framed incentive; b) loss aversion vs. no incentive; and c) gain-framed vs. no incentive.
- (c) **HIV re-testing uptake at 6-months:** We will compare the proportion of participants who retest for HIV at the 6-month study visit between the study groups. We will test for significant differences in HIV retesting uptake between the following groups using the 2-tailed  $\chi^2$  analysis or other appropriate statistical methods: a) loss aversion vs. gain-framed incentive; b) loss aversion vs. no incentive; and c) gain-framed vs. no incentive.
- (d) **HIV retesting uptake among deposit contract group participants who make deposits.** We will compare HIV retesting uptake as described for the Aim 3 primary analysis (above), but restrict the deposit contract group participants to the subset who make deposits at baseline and at the 3-4 month study visit. Since this subgroup is likely to be self-selected on the basis of their desire to come for retesting, we will determine the causal effect of the deposit contract on the likelihood of coming for

retesting using instrumental variables analyses in which randomization to the deposit contract group serves as an instrumental variable for a participant's decision to make a deposit.

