### 8.7.3 Sample Size & Accrual

We anticipate that about 30% of participants in the control group will come for retesting at both 3 and 6 months. With a sample size of 525 participants randomized 1:1:1 to the 3 study arms, we will have >80% power ( $\alpha=0.05$ , 2-sided) to show a difference of at least 15% in retesting rates in each of the intervention groups compared to the control group. With this sample size there will be >90% power to show a difference of at least 18% between the intervention and control groups.

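### Aim 3 secondary analysis (d): the between-arm test restricted to participants with both deposits conditions on half of its own outcome

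*Protocol*

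**What the plan says.** The primary outcome in 8.7.2 is retesting uptake, "defined as the proportion of participants retesting for HIV at both 3- and 6-month study visits". Secondary analysis (d) repeats that comparison across arms but would "restrict the deposit contract group participants to the subset who make deposits at baseline and at the 3-4 month study visit". No matching restriction is placed on the gain-framed or no-incentive arms.

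Section 8.4 fixes who can make a second deposit: "Participants who attend the 3-month visit and retest HIV negative will be asked if they would like to make a second deposit". The same section lets a participant who declined at baseline make a first deposit at 3-4 months, again only on coming to retest.

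Item (d) carries its own caveat, "Since this subgroup is likely to be self-selected on the basis of their desire to come for retesting", and adds a causal analysis in which "randomization to the deposit contract group serves as an instrumental variable" for the decision to deposit.

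Section 8.6 defines the matching secondary outcome more widely, covering participants "who agree to make a baseline deposit, a 3-4 month deposit, and those who agree to make a deposit at both study baseline" as well as the later visit. That makes three subsets, of which 8.7.2(d) carries one into a between-arm test.

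**The concern.** Membership of the analysed subset depends on part of the outcome. Someone in the deposit arm who did not retest at 3 months cannot make a second deposit, so that failure leaves the deposit arm's denominator. The same failure in the other arms stays in theirs. The resulting gap is separate from the self-selection that the protocol mentions: it arises even if the decision to deposit has nothing to do with motivation. Motivated depositing would normally add to it.

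What is at stake is a listed secondary result on people who take up the contract. Reported as a χ² test beside the primary comparison, it could be read as evidence that deposit contracts work when the difference comes from how the subset was formed.

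**Working it through.** **The plan's own figures.** With 525 participants randomized 1:1:1 there are 175 per arm. Section 8.7.3 assumes "about 30% of participants in the control group will come for retesting at both 3 and 6 months". At two-sided α = 0.05 with pooled variance, power is 82.9% for 30% vs 45% and 93.6% for 30% vs 48%. Both power statements (>80% for 15 points, >90% for 18 points) reproduce, so 15 to 18 points is a fair yardstick for the bias.

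**Inputs for the no-effect case.**
- P(retest at both visits) = 0.30 in both arms (8.7.3).
- p3 = P(retest at 3 months). The protocol gives no value, so this is an assumption, shown over a range.
- Uptake of each deposit: 90% as the main value (Section 2 reports more than 90% making deposits in the pilot), and 50% as a sensitivity value.
- Depositing is unrelated to the tendency to retest.

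**Formula.** Among those with both deposits, 3-month success is 100%, so their expected success at both visits is P(6 months | 3 months) = 0.30/p3. The spurious difference from control is 0.30/p3 − 0.30, which is positive for every p3 below 100%. The expected subset size is 175 × (baseline uptake) × p3 × (second uptake); for example, 175 × 0.9 × 0.5 × 0.9 ≈ 71.

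**Results.** False rejection at two-sided 5% comes from 4,000 simulated trials per row, testing the subset against the full control arm of 175.

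| Assumed p3 | Rate in subset | Spurious difference | False rejection, 90% uptake of each deposit | False rejection, 50% uptake of each deposit |
|---|---|---|---|---|
| 50% | 60% | +30 points | 99% | 78% |
| 54.8% (independent visits) | 55% | +25 points | 96% | 66% |
| 60% | 50% | +20 points | 88% | 54% |
| 70% | 43% | +13 points | 58% | 30% |
| 80% | 37.5% | +7.5 points | 26% | 15% |

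The spurious difference exceeds 15 points when p3 is below 0.30/0.45 = 66.7%, and 18 points when p3 is below 0.30/0.48 = 62.5%.

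**Check on the cause.** In the same simulations, comparing baseline depositors with the full control arm gave a difference of about 0 and about 5% rejection. The bias therefore comes from requiring the second deposit.

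**IV under no effect.** The ratio estimate (intention-to-treat, ITT, difference divided by the proportion depositing) was centred between −4 and 0 points across all scenarios. This held even with both deposits as the denominator. The ITT test behind it rejected in 5-6% of runs.

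**IV under a true effect, by exposure coding.** Take a 15-point ITT effect.
- Baseline deposit as exposure: 0.15/0.90 = 0.167, about 17 points.
- Both deposits as exposure, with p3 = 60%: 0.9 × 0.6 × 0.9 = 0.486, and 0.15/0.486 = 0.309, about 31 points. Exclusion also fails here, because a baseline deposit can change behaviour in people who never make the second one.

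**IV if applied against the gain-framed arm.** A participant who declines a baseline deposit "will not receive any incentive for the return HIV test at 3-4 months", whereas the same person in the gain-framed arm would have been offered a reward. Assignment then acts directly on decliners. As an illustration with assumed rates, let depositors retest at 60% vs 52% (true effect 8 points) and decliners at 30% vs 45%. At 90% depositing the ITT difference is 0.9 × 8 − 0.1 × 15 = 5.7 points, and 5.7/0.9 = 6.3 points instead of 8.

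**The case against.** The strongest reply is that the protocol does not rest its causal claim on the restricted comparison. Item (d) says the subset is likely self-selected and assigns the causal effect to the IV analysis, which is about zero when deposits do nothing. That stands. A reader might infer that the whole depositor analysis would show a benefit from ineffective deposits; the documents do not support this, and the bias belongs to the restricted test alone. The caveat does not rescue that test, however. It names the desire to retest, not the fact that membership guarantees the 3-month success, and the test remains planned.

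A reader might also infer that the IV estimate is inflated or invalid as planned. The text does not establish either. It speaks of a decision to make a deposit, in the singular, and does not define exposure as both deposits. The IV sentence names no comparator. Inflation and the gain-arm bias are conditional on choices that an analysis plan may settle, so both should be put as points to state clearly.

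Nor is a false positive close to certain in general. It is so only for low p3 with high deposit uptake; at p3 = 80% the false rejection rate is 26% or 15%.

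Finally, Section 8.6 names baseline depositors as a subset, and they do not have the 3-month success built in. This is a fair point, but 8.7.2(d) does not carry that subset into its test. The other two subsets in Section 8.6 share the defect.

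**Conclusion.** The restricted between-arm comparison in 8.7.2(d) is wrong as written, because it conditions on half of its own outcome in one arm only. With no deposit effect, a 30% control rate and depositing unrelated to motivation, the spurious difference runs from about +30 points (p3 = 50%) to +7.5 points (p3 = 80%). False rejection is 99% to 26% at 90% uptake of each deposit, and 78% to 15% at 50% uptake. The direction follows from Sections 8.4 and 8.7.2 alone; the size rests on p3, which the protocol does not give.

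The IV analysis is sound under the null but does not validate the restricted test. Its behaviour under a true effect depends on an exposure and a comparator that should be stated.

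Severity is moderate. This is one secondary analysis; the primary comparison, the separate 3- and 6-month comparisons and the sample size are unaffected.

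**What to change.** In Protocol 8.7.2(d):

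1. Delete the between-arm test restricted to participants with both deposits. Report retesting among second depositors descriptively only.
2. Reconcile 8.7.2(d) with the three depositor subsets in Section 8.6, noting that any subset defined by a 3-4 month deposit has 3-month success built in.
3. State that the IV exposure is the baseline deposit decision and that the IV comparator is the no-incentive arm. Note that first deposits made at 3-4 months by baseline decliners slightly strain the exclusion assumption for the both-visit outcome.
4. Leave loss aversion versus gain-framed to the ITT comparison.

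The cost is wording only. No new data are needed, and the sample size and primary analysis do not change.

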### 8.6 Outcome measures

#### Primary outcome:

- a) **HIV retesting uptake at 3 and 6 months.** The primary outcome will be defined as the proportion of participants who retest for HIV at a study venue at both 3- and 6-month study visits. Successful retesting uptake will be defined as accessing HIV testing at a study-testing site (see Section 8.6.1 below) within 3-4 months and 6-7 months of randomization. We will use electronic fingerprint biometric measurements that link participants in real-time to a study ID at the time of HIV testing to determine whether study participants tested for HIV or not. Retesting outside of the pre-specified testing “windows” will not be considered as successful HIV retesting uptake.

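### Aim 3 secondary analysis (d): the both-deposits subset has already met the 3-month half of its outcome, so the restricted comparison with whole arms is biased towards deposits

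*Protocol*

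**What the plan says.** The Aim 3 primary outcome (Protocol 8.6) is "the proportion of participants who retest for HIV at a study venue at both 3- and 6-month study visits". Secondary analysis (d) in 8.7.2 takes over the comparison set out for the primary analysis, so it uses this same outcome. In the deposit arm, however, it will "restrict the deposit contract group participants to the subset who make deposits at baseline and at the 3-4 month study visit". It states no matching restriction for the other two arms.

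Section 8.4 fixes who can make the later deposit. For baseline depositors: "Participants who attend the 3-month visit and retest HIV negative will be asked if they would like to make a second deposit". Those who declined at baseline but "come for retesting at the 3-4 month visit, will have an opportunity to make a deposit" at that visit. Either way, the 3-4 month deposit comes after a 3-4 month retest.

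Secondary outcome d) in 8.6 lists three depositor sets: those depositing at baseline, those depositing at 3-4 months, and "those who agree to make a deposit at both study baseline and the 3-4 month study visit". Analysis (d) carries forward only the last.

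The same item adds a caveat and a remedy. The caveat begins "Since this subgroup is likely to be self-selected on the basis of their desire to come for retesting". The remedy is an analysis in which "randomization to the deposit contract group serves as an instrumental variable" for the participant's decision to deposit.

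**The concern.** The subset is defined partly by the outcome. A deposit-arm participant who misses the 3-month retest cannot make the second deposit and drops out of the comparison. A control or gain-framed participant who misses it stays in and counts as a failure. This goes beyond the motivational self-selection that the protocol names: one of the two outcome components is guaranteed in one arm only, and adjusting for motivation would not remove that.

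At stake is a planned, tested comparison that could show a clear depositor advantage over control, and likewise over gain-framed incentives, when deposits have no effect.

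**Working it through.** **Inputs from the protocol.** Section 8.7.3 gives 525 participants randomised 1:1:1 (175 per arm), a control rate of about 30% for retesting at both visits, and two-sided alpha of 0.05. Section 2 reports that more than 90% of the pilot's deposit group made deposits.

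**Assumptions.** The 3-month retest rate a is not stated and is varied. Take-up of the second deposit is not stated either. The main case takes 90% for each deposit, the other case 50% for each. Deposit take-up is assumed unrelated to later retesting. The exclusion of people who test positive at 3 months is ignored as minor.

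**Reproducing the plan's power.** The two-proportion formula uses the pooled variance under the null and the unpooled variance under the alternative. For 30% against 45%, n = 175 per arm:
- null SE = √(2 × 0.375 × 0.625 / 175) = 0.0518
- alternative SE = √((0.21 + 0.2475) / 175) = 0.0511
- power = Φ((0.15 − 1.96 × 0.0518) / 0.0511) = 82.9%

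The same formula gives 93.6% for 30% against 48%. Both agree with the stated bounds (>80% and >90%).

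**Restricted comparison when deposits do nothing.** Every arm has P(both visits) = 0.30. Everyone in the subset has retested at 3 months, so its both-visits rate is P(6 m | 3 m) = 0.30/a. The expected subset size is 175 × a × (baseline take-up) × (second take-up). At a = 0.6 with 90% take-up of each deposit, this is 175 × 0.6 × 0.81 = 85 people, at 0.30/0.60 = 50%, against 175 controls at 30%. The power formula with these unequal sizes gives rejection of 88%.

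| a | Subset rate | Spurious difference | Subset n (90% each) | False positives (90% each) | False positives (50% each) |
|---|---|---|---|---|---|
| 0.4 | 75% | +45 | 57 | about 100% | 96-98% |
| 0.5 | 60% | +30 | 71 | 99% | 79% |
| 0.6 | 50% | +20 | 85 | 88% | 52-53% |
| 0.7 | 43% | +13 | 99 | 57% | 30% |
| 0.8 | 37.5% | +7.5 | 113 | 27% | 15-16% |
| 0.9 | 33% | +3 | 128 | 9-10% | 6-7% |

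Simulation (4,000 trials per setting) agrees with the formula; ranges span the two methods. The spurious difference exceeds the 15 points the trial is powered for whenever 0.30/a > 0.45, that is a < 0.30/0.45 = 0.67.

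The gain-framed comparison is biased in the same way. If both incentive arms had 60% at 3 months and 45% at both visits (assumed), the subset would show 0.45/0.60 = 75% against 45%.

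**Same null, other analyses.** Comparing whole randomised arms gave rejection of 4.7-5.6%. Restricting on the baseline deposit alone gave 4.5-5.5%, under the assumption that depositing is unrelated to propensity to test.

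**Instrumental-variable (IV) estimate.** It equals the intention-to-treat difference divided by the difference between arms in the share exposed. Under the null the numerator has expectation zero. The simulated mean, even with both deposits as the exposure, was −0.05 to +0.002, which is ratio noise and no spurious benefit.

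Now assume a real intention-to-treat effect of 15 points, 90% take-up of each deposit, and 55-80% retesting at 3 months in the deposit arm:
- exposure = both deposits: 0.15 / (0.9 × 0.55 × 0.9) = 0.337, down to 0.15 / (0.9 × 0.80 × 0.9) = 0.231
- exposure = baseline deposit: 0.15 / 0.9 = 0.167
- exposure = any deposit: first stage 0.9 + 0.1 × a × 0.9 = 0.950 to 0.972, giving 0.158 to 0.154

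The first line is inflated because people who deposited at baseline only are counted as unexposed, although their deposit was at stake at the 3-month retest. That breaks the exclusion restriction.

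**The case against.** The strongest reply is that item (d) does not rest on the restricted comparison. It concedes self-selection in the next sentence and takes the causal effect from an IV analysis based on randomisation. This stands as far as it goes. A reader might infer that the trial would report a causal deposit effect even if deposits did nothing. The protocol does not support that, because the IV estimate is null when deposits and their offer have no effect.

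A reader might also infer that the IV estimate will be well above the truth. That needs the exposure to be both deposits. The protocol speaks of a decision to make a deposit, in the singular; read as any deposit, a 15-point effect becomes about 15-16 points. The wording is ambiguous, since it follows directly on a subset defined by both deposits, but the exact exposure is a detail commonly left to a statistical analysis plan.

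The size is also uncertain. The protocol gives neither the 3-month rate nor the second-deposit take-up, and the pilot's >90% does not describe a second deposit at a retest visit. With 3-month retesting of 80-90% the bias is small.

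Finally, restricting to baseline depositors does not make a randomised comparison: they are still self-selected, and the 4.5-5.5% above assumes that away.

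None of this rescues the restricted comparison itself. The protocol fixes its subset, and naming motivation as the selection mechanism does not tell the reader that half of the outcome is guaranteed.

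**Conclusion.** The restricted comparison in 8.7.2(d) is wrong as written. By the protocol's own rules, only people who have already retested at 3-4 months can enter the subset, and the comparison arms carry no such condition. The bias in favour of deposits follows from those definitions. Its size rests on the assumed 3-month rate and deposit take-up: large for a up to about 0.7, modest at 0.8 and slight at 0.9.

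The reach is limited. The primary analysis and secondary analyses (b) and (c) compare whole randomised groups and are unaffected, as is the power statement. The IV analysis needs its exposure named; it is not shown to be wrong. This should be fixed, but it does not threaten the trial's main conclusion.

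**What to change.** In 8.7.2(d):
- Replace the both-deposits subset with the baseline-deposit subset already listed under secondary outcome d) in 8.6. That deposit precedes any retest. Label the comparison descriptive, because depositors remain self-selected.
- State that the IV exposure is the baseline deposit and that 3-4 month retesting is the main IV outcome. No second deposit can have acted by then.
- If the both-visits outcome is kept for the IV analysis, use any deposit as the exposure, or note that baseline decliners may deposit at 3-4 months.
- Report the second deposit only against 6-7 month retesting, with all three arms limited to participants who retested HIV-negative at 3-4 months, labelled non-randomised.

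Align the wording of 8.6 d) with this. The cost is a text change to two items, with no new data, no extra participants and no change to the intervention.

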## **8.6.1 HIV Testing**

### **8.6.1.1 Testing Venues**

We will measure HIV testing at one or more venues within each study community. These may include the community's government-run health facility or at mobile testing sites established by our study (see Section 5.6.1). HIV testing uptake will be recorded at baseline and over a period of up to 12 months after enrolment and randomization, in order to allow for follow up testing of participants who do not retest within 7 months of randomization.

At the time they are enrolled in the study, all participants will receive information on when and where to find the testing venues where HIV retesting uptake will be recorded.

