Post-test Questionnaire: Participants who come for repeat testing (i.e. 3-4 months and 6-7 months after baseline HIV testing) will be asked to participate in a questionnaire to understand their reasons for retesting. Participants who do not retest for HIV at the 6-month study visit will be contacted, and visited at home or a place of their choosing, and asked to participate in a short questionnaire to understand their reasons for not retesting and to offer follow-up HIV testing, within 12 months of randomization.

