- (e) **Cumulative HIV incidence:** We will compare the proportion of participants who test HIV antibody positive within 7 months of participant randomization in each of the study groups using 2-tailed  $\chi^2$  tests or other appropriate statistical methods. We hypothesize that the proportion of newly diagnosed HIV antibody positive participants will be higher in the control group, due to failure to participate in retesting for HIV.

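### Aim 3's HIV incidence comparison counts only infections found by retesting within 7 months, so its stated hypothesis of more new diagnoses in the control arm contradicts its own case definition

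*Protocol*

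**What the plan says.** Section 8.6 of the protocol, secondary outcome (e) for the Aim 3 trial, is framed as infection: "We will compare the cumulative incidence of HIV infections in each study group over the 6-7 months of study participation following randomization".

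Section 8.7.2(e) puts it into operation as diagnosis: "We will compare the proportion of participants who test HIV antibody positive within 7 months of participant randomization in each of the study groups", using two-tailed chi-square tests or other appropriate methods. It then hypothesises that "the proportion of newly diagnosed HIV antibody positive participants will be higher in the control group, due to failure to participate in retesting".

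Three other places bear on this:

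- The primary outcome (8.6) is "the proportion of participants who retest for HIV at a study venue at both 3- and 6-month study visits". Section 8.7.2 hypothesises that it will be higher with loss aversion incentives than with no incentive.
- Section 8.7.3 states: "We anticipate that about 30% of participants in the control group will come for retesting at both 3 and 6 months". It sizes the trial for a difference of at least 15 percentage points between each incentive arm and control.
- Testing is recorded for up to 12 months, "in order to allow for follow up testing of participants who do not retest within 7 months of randomization" (8.6.1.1). Participants who miss the 6-month retest are contacted, among other reasons "to offer follow-up HIV testing, within 12 months of randomization" (8.6.1.2).

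**The concern.** The outcome is named as infections, but the analysis counts infections that a test has revealed by month 7. Those are the same only if everyone is tested, or if testing is equally complete in every arm. The trial is built to make testing unequal between arms, so the better the incentives work, the more the arms differ in their chance of detecting an infection.

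The hypothesis then runs against the case definition. Failure to retest is given as the reason why control participants should be diagnosed more often. Within the 7-month window it can only reduce the number diagnosed.

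What is at stake is interpretation. A lower count in control could be read as lower risk, and a higher count under incentives as an excess of infections, when either could reflect how many people were tested. Tests done after month 7 in people who had not retested bear directly on the missing infections, but they fall outside the cut-off.

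**Working it through.** **Inputs from the protocol.** 525 participants randomised 1:1:1, so 525 / 3 = 175 per arm (8.7.3). Retesting at both visits: 30% in control, and 30% + 15 = 45% or 30% + 18 = 48% with incentives (8.7.3). Two-sided alpha is 0.05.

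**Inputs not in the protocol (assumptions).** True cumulative HIV incidence by 7 months, taken as 1–5% and equal in the two arms. Share tested at least once by 7 months, taken either as 50% vs 65%, or as 30% vs 45% by using the both-visits planning rates as a proxy.

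**The plan's own figure.** The protocol gives no power for the incidence comparison. Its power for retesting reproduces, using the normal approximation with pooled variance under the null and no continuity correction:

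- 30% vs 45%: pooled proportion 0.375; z = [0.15 − 1.96 × √(2 × 0.375 × 0.625 / 175)] / √[(0.30 × 0.70 + 0.45 × 0.55) / 175] = 0.95, so power is 82.9% (stated: above 80%).
- 30% vs 48%: the same formula gives z = 1.52 and power 93.6% (stated: above 90%).

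The difference in testing that drives the detection problem is therefore the one the trial is sized to show.

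**Expected diagnoses.** To a first approximation, diagnosed proportion = true incidence × share tested by 7 months. With equal true incidence, the incidence cancels from the ratio between arms:

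- 50% vs 65% tested: 0.65 / 0.50 = 1.3
- 30% vs 45% tested: 0.45 / 0.30 = 1.5
- 30% vs 48% tested: 0.48 / 0.30 = 1.6

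| True incidence (both arms) | Tested, control vs incentive | Diagnosed | Expected cases per 175 |
|---|---|---|---|
| 1% | 30% vs 45% | 0.30% vs 0.45% | 0.53 vs 0.79 |
| 2% | 30% vs 45% | 0.60% vs 0.90% | 1.05 vs 1.58 |
| 5% | 30% vs 45% | 1.50% vs 2.25% | 2.63 vs 3.94 |
| 2% | 50% vs 65% | 1.00% vs 1.30% | 1.75 vs 2.28 |

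For the stated hypothesis to hold in expectation, true incidence in control would have to exceed that in the incentive arm by more than the same factor of 1.3 to 1.6.

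**Would the bias be seen?** Take independent binomial counts of 175 per arm at 1.0% vs 1.3% diagnosed. The incentive arm shows more cases in about 50% of trials, the arms tie in about 20%, and the incentive arm shows fewer in about 30%. The uncorrected chi-square test rejects in about 5% of trials.

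**The case against.** **The endpoint is minor and sparse.** It is the last-listed secondary analysis, the test is two-tailed so the hypothesised direction does not enter it, and nothing in the primary analysis or sample size depends on it. This stands, and it sets the severity.

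**The incentives would not visibly raise incidence.** A reader might infer that, if the incentives work, the trial will report an apparent increase in HIV infections or hide a real preventive effect. The documents do not support that. With half a case between the arms in the 2% example, the excess appears only about half the time and is rarely significant. So few cases could demonstrate little under any ascertainment rule. The bias is in expectation only.

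**The magnitude is assumed.** This also stands. The 30% and 45% refer to testing at both visits, and 50% vs 65% appears nowhere in the protocol. With those last figures one can derive that incentives would have to cut true infection by 1 − 50/65 = 23% merely to show equal diagnosed proportions, but that number is no firmer than its inputs. The formula also treats any test by month 7 as finding every infection to month 7, although a test at 3–4 months cannot reveal a later infection. It further assumes that testing is unrelated to infection risk.

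**The 7-month horizon is defensible, and late tests are no simple cure.** Catch-up testing is only offered, its uptake is unstated, and it can find infections acquired after month 7. Adding those tests to a crude proportion would introduce a new bias towards the arm with more non-retesters. This stands and shapes the fix.

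**The wording leaves room.** The allowance for other appropriate methods frees the choice of test, but not the case definition or cut-off. If the denominator were testers only, the mechanical undercount would go. However, 8.7.2(e) says participants, where the parallel pilot analysis (7.7.2) says HIV testers. Selection into testing would in any case still differ by arm. The hypothesis might make sense for infections still undiagnosed at month 7 or found later, but the section defines neither. These points do not rescue the text.

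**Conclusion.** The point holds as a moderate error of definition and interpretation in a secondary analysis. An outcome named as incidence of infections is measured as diagnoses by month 7. Detection depends on the behaviour that the arms are meant to change, and the stated hypothesis gives a reason that works in the opposite direction.

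The expected direction rests on two conditions: equal true incidence, and more participants tested at least once in the incentive arms, which the primary hypothesis makes likely. It does not depend on the level of incidence. The size, a ratio of roughly 1.3 to 1.6, is illustrative.

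**What to change.** 1. In 8.6(e) and 8.7.2(e), relabel the 7-month proportion per participant randomised as HIV diagnosis yield. Correct the hypothesised direction or delete it.
2. If incidence is to be compared, define it separately, using all study tests up to 12 months including the catch-up tests of 8.6.1.1 and 8.6.1.2. Use a method that accounts for test timing, either interval-censored time to infection or person-time to the last test, because a late test can detect an infection acquired after month 7.
3. Report the share never retested, by arm, beside both results.

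The cost is a wording change and a little more analysis. The protocol already plans the tests, so no new visits are needed. Uptake of catch-up testing may itself be incomplete or differ by arm, so the incidence comparison would still need that caveat.
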